Recently, a hypothesis has been suggested that vitamin-D deficiency can alter the composition of intestinal bacteria. A recently published observational study has shown a link between dietary intake of vitamin D and intestinal bacteria [22]. In mouse models, it has also been observed that vitamin D can alter the intestinal microbiota population into a beneficial bacterium [23]. It also seems that vitamin D plays a role in regulating the immune system in the gut, and its deficiency may change the function of the intestinal wall, leading to transfer of endotoxins, like lipopolysaccharides (LPSs), into the bloodstream, which itself causes the development of inflammation [24]. Animal studies have also shown that vitamin D reduces dysbiosis, infection, permeability of the intestinal epithelial duct and ultimately deacreases the incidence of inflammatory bowel diseases, like Crohn’s disease, by maintaining the hemostasis of the intestinal epithelium cells and tight-junction structures [23, 25, 26].

Vitamin D level is largely dependent on exposure to ultraviolet sun rays (wave-length of 290–315 nm). However, various environmental, cultural, social, and individual factors can affect the amount of ultraviolet B (UVB) that reaches the skin. On the other hand, dietary sources of vitamin D are too rare. Therefore, supplementation and fortification are the only ways to achieve the amount of vitamin D required. Supplement consumption is challenged because of population coverage, people’s compliance, cost, and regular consumption of supplements [27]. In contrast, using fortified foodstuffs has the advantage of lower cost and higher compliance [28]. Then, vitamin-D fortification seems to be a better startegy to prevent or treat vitamin-D deficiency. In this study we will fortify bread with vitamin D, because it is available to people with moderate to severe food-insecurity households and its use is not significantly related to socioeconomic factors such as income and education. Also, according to the latest survey of the national food pattern in Iran, the average consumption of bread is more than 300 g per day,while milk intake,another current food that is fortified, is only 38 g per day [29]. In addition, bread is a staple food which is consumed routinely in all meals by the Iranian population.

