#### Primary objective

To compare within- and between-group variations in circulating 25(OH) D levels.

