#### Participant recruitment

In this trial, we will recruit a total of 90 participants (each group 30 subjects) from apparently healthy subjects of Tehran, the capital city of Iran. Participant recruitment was expected to commence by September 2018, and the trial is due to last 20 months. This assumes 4 months for participants recruitment, 4 months for run-in periods and intervention, 2 months for laboratory testing, 2 months for data collection, preparing and entering into SPSS software, 3 months for data retrieval and analysis, and 4 months to write the study report. A Standard Protocol Items: Recommendations for Interventional Trials (SPIRIT) Checklist [32] was used to report this protocol (Additional file 1, SPIRIT Checklist). Table 1 also shows the trial schedule. Before collecting any information, informed consent will be obtained from all participants. After reviewing the consent forms and answering any probable questions by study staff, those who are interested will be asked to sign the forms. A copy of the consent form will be gave to participants and all original signed consent forms will be kept by the study staff (Additional file 2, consent form).

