### Statistical analyses

Data analysis will be done using SPSS version 21 software. To describe the quantitative data, the mean and standard deviations will be used and to describe the qualitative data absolute and relative abundance will be used. To compare absolute or relative abundance the chi-square or Fisher’s exact statistics will be used. As the data should compare groups, between groups, and between-group changes, and to reduce the probability of the error, an analysis of two-way variance with repeated measures will be used to explore the impact of time and time-group effects with adjustment using the Bonferroni post-hoc test. The effects of the intervention in each group were examined using the paired *t* test versus the baseline values. Between-group comparisons were examined using analysis of variance (ANOVA) followed by a Bonferroni post-hoc analysis. Covariance analysis will be used to adjust the effects of confounding variables. The correlation between the three groups will be evaluated by Pearson (normal data distribution) or Spearman (abnormal distribution). The significance level in this study will be considered to be *p* < 0.05.

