### Trial status

The current protocol is version 1, dated 31 January 2017. The recruitment process will start on 1 July 2018 and is estimated to last for 6 months.

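### Within-arm paired t tests are labelled as tests of the intervention's effect and sit in the primary objective, and nothing says that the randomised comparisons, not these, decide efficacy

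*Protocol article*

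**What the plan says.** The Primary objective is "To compare within- and between-group variations in circulating 25(OH) D levels". The Secondary objectives use the same within-and-between form for all other outcomes. Neither objective ranks one comparison above the other.

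The Statistical analyses section lists several tests without ranking them:

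- "an analysis of two-way variance with repeated measures will be used to explore the impact of time and time-group effects", with Bonferroni adjustment;
- "The effects of the intervention in each group were examined using the paired" t test versus baseline values;
- "Between-group comparisons were examined using analysis of variance (ANOVA) followed by a Bonferroni post-hoc analysis";
- lastly, and with no covariate named, "Covariance analysis will be used to adjust the effects of confounding variables".

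On the endpoint, the Background states: "Vitamin D level is largely dependent on exposure to ultraviolet sun rays". Eligibility requires 25(OH)D below 50 nmol/L, and the Intervention section gives 12 weeks of bread. The calendar is given twice. Trial status says "The recruitment process will start on 1 July 2018 and is estimated to last for 6 months". The Participant recruitment section says "Participant recruitment was expected to commence by September 2018", with 4 months allowed for recruitment.

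**The concern.** The only test described as examining the intervention's effects is an uncontrolled before-after comparison inside each arm. A change within one arm is the sum of the bread's effect, any seasonal change over the 12 weeks, any regression to the mean after selection on a low value, and any other influence shared by all participants. The plain-bread arm exists to remove everything but the first of these, and the paired test does not use it.

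Season is a realistic threat here. The article itself says that vitamin D depends largely on sunlight, and both recruitment calendars carry most 12-week periods into autumn and winter. Because within-group change is in the primary objective, the paired test is more than a descriptive extra. A report that drew its conclusions from which arms changed significantly would still comply with the text. The same holds for the secondary outcomes.

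**Working it through.** **Inputs from the article.** 30 per group, 1:1:1; difference of 20 nmol/L; two-sided alpha 0.05; beta 0.2; 2-week run-in; 12 weeks of bread; recruitment July to December or September to December.

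**Inputs not in the article (assumptions).** The SD of change and the size and timing of seasonal drift.

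**Step 1: the plan's own figure.** No SD is stated, so n = 30 cannot be reproduced, only inverted. By the normal approximation, SD = 20 / [(1.960 + 0.842) × √(2/30)] = 27.6; by the exact t distribution it is 27.2. An SD of 20 would need 16 per group, 25 would need 25, and 30 would need 36. Below, 27.2 is the upper value, with 20 and 15 for range.

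**Step 2: direction and plausible size of drift.** Take a cosine curve with half-amplitude A and a peak in early September. Average the 84-day change over the entry window, starting 14 days after entry. The mean drift is about −0.83 A for July to December and −1.03 A for September to December. For A = 5, 10 and 15 nmol/L this gives about −4, −8 and −12, or −5, −10 and −15 nmol/L.

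**Step 3: one arm's paired t test with no treatment effect.** Noncentrality = drift / (SD/√30), 29 degrees of freedom, critical value 2.045. For SD 27.2 the standard error is 27.2/√30 = 4.97, so drifts of 5, 10 and 15 give noncentralities of 1.01, 2.01 and 3.02.

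| SD of change | no drift | drift 5 | drift 10 | drift 15 |
|---|---|---|---|---|
| 27.2 | 5% | 16% | 49% | 83% |
| 20 | 5% | 26% | 75% | 98% |
| 15 | 5% | 42% | 94% | about 100% |

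**Step 4: which way those rejections point.** At SD 27.2 and a drift of −5, significant falls occur in 16.2% of trials and significant rises in 0.17%. At −10 the figures are 49.5% and 0.005%. A false rise is therefore rarer than the nominal 2.5%.

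**Step 5: masking.** If fortified bread truly adds the planned 20 nmol/L and drift is −10, the fortified arm's own mean change is 20 − 10 = 10. At SD 27.6 its paired test then rejects in 48% of trials, against 97% without drift. The contrast with plain bread is still 10 − (−10) = 20.

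**Step 6: the randomised comparison under the same drift.** One-way ANOVA on change across the three arms, 20,000 simulated trials for each case, shifts of 0, 10 and 20 nmol/L, SD 20 and 27.6: rejection stays between 4.8% and 5.2%. With two time points, the time-by-group test is equivalent to this ANOVA.

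**The case against.** The strongest reply is that the same paragraph already plans the right analyses. The repeated-measures analysis with its time-by-group term comes first, the between-group ANOVA directly follows the paired-test sentence, and covariance analysis is added. The Sample size section powers the trial on a 20 nmol/L difference per treatment group and speaks of pairwise comparisons. The Discussion rests causal inference on the randomised, placebo-controlled design, and a sunlight questionnaire is collected. All of this stands: common drift cancels in those contrasts, as step 6 shows.

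Two stronger readings are therefore not supported. A reader might infer that efficacy will be judged by the paired tests alone; the article does not say so. A reader might also infer that season will pass for a benefit; under the recruitment calendars and an autumn-winter decline, the drift is downward and the false rejections are falls.

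A further temptation is to quote how often three identical arms would give discordant paired-test verdicts, 1 − p³ − (1 − p)³. At SD 27.2 this is 41%, 75% and 42% for drifts of 5, 10 and 15. At SD 15 it is 73%, 17% and 0.1%. It depends heavily on the assumptions, and on a decision rule that the article never states, so no single figure should be cited.

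Regression to the mean is also uncertain. Volunteers are screened at a laboratory and then enter a 2-week run-in. If baseline is a fresh sample, much of the regression precedes it.

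What the reply does not answer is that the wording attaches the intervention's effect to the paired test, that within-group change is in both sets of objectives, and that nothing subordinates either to the randomised contrasts.

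**Conclusion.** The point holds in a limited form. The article states a test of the intervention's effect that cannot isolate that effect, and places the same comparison in the primary objective. Valid randomised comparisons are planned beside it, but it is not stated that they alone decide efficacy.

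For common drifts of 5 to 10 nmol/L with no treatment effect, the paired test rejects in 16% to 49% of trials at SD 27.2 and in 42% to 94% at SD 15, while the between-arm test stays near 5%. These figures rest on an SD back-solved from n = 30, or lower assumed values, and on assumed drifts, since the article gives neither. The likely harm from an autumn-winter decline is a hidden benefit or an apparent fall on plain bread. Regression to the mean would push the other way, by an amount that the article does not allow one to fix. That a within-arm p-value does not measure the effect of the bread depends on none of these assumptions.

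**What to change.** Three wording changes:

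1. In the Primary and Secondary objectives, replace the within-and-between comparison with the between-group difference in change from baseline.
2. In Statistical analyses, state that efficacy conclusions rest only on the randomised contrasts with plain bread. Name which planned analysis carries the primary outcome: the time-by-group term, or covariance analysis of the 12-week value with baseline as covariate.
3. Describe within-arm change as descriptive, reported as a mean with 95% CI, and remove the paired t test as a test of the intervention's effect.

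No data, visit or sample size changes. The cost is that the objective loses a within-arm significance claim, which could not support a causal conclusion anyway.

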#### Sample size

Based on data on serum 25(OH) D changes from Nikooyehet al [33]., to achieve 20 nmol/L difference in circulating 25(OH) D with a two-sided alpha of 0.05 and a beta of 0.2 after a 12-week intervention period, the target sample size will be 30 individuals per treatment group. We are not adjusting the primary outcome comparisons for the multiple pairwise comparison.

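### No between-group analysis of 25(OH)D is named as primary, the ANOVA's response is not stated, and baseline 25(OH)D is not a stated covariate; one baseline-adjusted ANCOVA would settle all three

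*Protocol article*

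**What the plan says.** The primary objective in the protocol article is "To compare within- and between-group variations in circulating 25(OH) D levels". It names no single contrast and no response variable.

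The Statistical analyses section then lists four procedures for continuous outcomes:

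- a repeated-measures model: "an analysis of two-way variance with repeated measures will be used to explore the impact of time and time-group effects", with Bonferroni post-hoc tests;
- paired t tests against baseline within each arm;
- for comparing arms: "Between-group comparisons were examined using analysis of variance (ANOVA) followed by a Bonferroni post-hoc analysis";
- for adjustment: "Covariance analysis will be used to adjust the effects of confounding variables".

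All are read at the 0.05 level. The section does not say which one answers the primary question, whether the ANOVA is run on 12-week values or on changes, or which covariates enter the ANCOVA.

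The Sample size section plans "to achieve 20 nmol/L difference in circulating 25(OH) D" "with a two-sided alpha of 0.05 and a beta of 0.2", with 30 per arm. It cites its source as "Based on data on serum 25(OH) D changes" and gives no SD.

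**The concern.** Blood is sampled at baseline and after 12 weeks, so each participant has a baseline and a final 25(OH)D. Three of the four procedures can each produce a between-arm p value from these data: the time-by-group test, the ANOVA and the ANCOVA. With no order among them, the reported answer may depend on which is chosen.

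The ANCOVA is offered only as a remedy for confounding. In a 1:1:1 randomised trial, allocation deals with confounding in expectation. The main uses of ANCOVA here are precision and correction for chance imbalance at baseline, and the covariate that serves both best, baseline 25(OH)D, is not named. What is at stake is some power in a trial of 90 people and the credibility of a result picked from several.

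**Working it through.** **1. Which tests coincide.** With two time points, the time-by-group F test of a repeated-measures ANOVA is the one-way ANOVA of the change score. If the separate ANOVA is also on change, the two are one test. If it is on 12-week values, they differ.

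**2. The plan's own figure.** No SD is given, so n = 30 can only be solved backwards from a difference of 20 nmol/L, two-sided alpha 0.05 and power 80%.

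- Normal approximation: SD = 20/(1.960 + 0.842) × √(30/2) = 27.65.
- Noncentral t: SD ≈ 27.2 (power 80.0% at 27.2).

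I use 27.2 below. The documents do not say whether it would be the SD of 12-week values or of change.

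**3. Variance formulas.** Let s be the SD at 12 weeks, b the SD at baseline and r their correlation. None is given; r = 0.3 to 0.7 is an assumption.

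- ANOVA on 12-week values: s²
- ANOVA on change: s² + b² − 2rsb, which is 2s²(1 − r) when b = s
- ANCOVA with baseline: s²(1 − r²)

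The ANCOVA variance is in large samples no greater than either of the others. The price is one residual degree of freedom.

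**4. Equal variances (b = s).** Reduction in variance with ANCOVA:

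| r | vs 12-week values: r² | vs change: 1 − (1 + r)/2 |
|---|---|---|
| 0.3 | 9% | 35% |
| 0.5 | 25% | 25% |
| 0.7 | 49% | 15% |

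**5. Narrow baseline.** Entry requires 25(OH)D below 50 nmol/L, so the baseline spread may be small. Assume b = 10 and s = 20 or 27:

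| r | s | change variance | ANCOVA variance | reduction |
|---|---|---|---|---|
| 0.3 | 20 | 380 | 364 | 4.2% |
| 0.3 | 27 | 667 | 663.4 | 0.5% |
| 0.5 | 20 | 300 | 300 | 0% |
| 0.5 | 27 | 559 | 546.8 | 2.2% |
| 0.7 | 20 | 220 | 204 | 7.3% |
| 0.7 | 27 | 451 | 371.8 | 17.6% |

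So the gain over change scores is about 0–4% at r = 0.3 to 0.5 and 7–18% at r = 0.7. Against 12-week values it is still r², that is 9–49%.

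**6. Power at 30 per arm, difference 20, two-sided 0.05 (noncentral t).**

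*If 27.2 is the unadjusted 12-week SD*, the ANCOVA SD is 27.2 × √(1 − r²):

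- r = 0.3: 25.9, power 84%
- r = 0.5: 23.6, power 90%
- r = 0.7: 19.4, power 98%

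*If 27.2 is the SD of change and b = 10*, solving s² − 20rs + 100 = 27.2² gives s = 10r + √(100r² + 639.84):

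- r = 0.3: s = 28.5, ANCOVA SD 27.2, power 80%
- r = 0.5: s = 30.8, ANCOVA SD 26.7, power 82%
- r = 0.7: s = 33.2, ANCOVA SD 23.7, power 89%

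**7. Does the choice of test matter?** A null simulation (three arms of 30, equal variances, 20,000 runs for each r) ran three overall F tests: 12-week values, change and baseline-adjusted ANCOVA. Each rejected in about 5% of runs. At least one rejected in 9.4%, 10.1% and 10.2% at r = 0.3, 0.5 and 0.7, and the three disagreed in 8–10%. This applies only if the stated ANOVA is on 12-week values and the ANCOVA includes baseline.

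**The case against.** The strongest reply is that the plan does not ignore baseline. The response of the ANOVA is not stated; the sample size rests on changes, and the analysis section itself refers to changes between groups. A change-score ANOVA is therefore at least as natural a reading, and it uses baseline. The repeated-measures model uses it as well, and the ANCOVA could. This stands. A reader might infer that the named test leaves baseline out and carries chance baseline differences into the result; the text supports that only on the 12-week-value reading.

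On the change reading, the ANOVA and the time-by-group test are the same test, so there are fewer competing tests than the list suggests. The paired t tests answer the within-arm question, which is part of the stated objective, and are not a further test between arms. A reader might also infer an error rate near 10%. That figure assumes three distinct tests and a report of whichever is significant, and the protocol states neither.

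A headline gain from 80% to 90% power is likewise tempting. It needs r = 0.5 and 27.2 as the unadjusted 12-week SD. If 27.2 is the SD of change and the baseline SD is 10, power at the same r is 82%.

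Finally, covariate lists and the naming of a primary model are often left to an analysis plan, and change-score ANOVA is a valid method. That is fair as far as missing detail goes. But the article is not silent: it assigns the comparison of arms to ANOVA and reserves ANCOVA for confounders. That assignment is what should change.

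**Conclusion.** The point holds as a matter of precision and pre-specification. No listed method is invalid. No between-group analysis of 25(OH)D is primary, the response of the ANOVA is undefined, and baseline 25(OH)D is not a stated covariate. On either reading of the ANOVA, a baseline-adjusted ANCOVA is in large samples at least as precise and leaves one answer.

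The size is uncertain because every input is assumed. The variance gain is substantial against 12-week values (9–49%). Against change scores it runs from nothing (narrow baseline, r = 0.5) to 35% (equal variances, r = 0.3). Power rises from 80% to between 80% and 98% across the two readings of the implied SD. The case for the change does not need the upper end of that range, because the change costs nothing and fixes the primary test in advance.

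**What to change.** In the Statistical analyses section, before unblinding:

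- Name one primary between-group analysis: ANCOVA of 12-week 25(OH)D on arm with baseline 25(OH)D as covariate, reporting adjusted differences between arms with 95% confidence intervals.
- Use the same model, with the outcome's own baseline value, for each continuous secondary outcome.
- Make the repeated-measures and one-way ANOVAs sensitivity analyses, and state the response of the latter.
- Make the paired t tests descriptive.
- Replace the open reference to confounders with a fixed covariate list.

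Calendar month of sampling may be added, since the Background notes that "Vitamin D level is largely dependent on exposure to ultraviolet sun rays", but it is optional and the fix does not depend on it.

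The cost is wording only. Baseline 25(OH)D is measured in every participant, and SPSS fits the model. No extra participants, visits or assays are needed.

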### Discussion

In the last decade, attention has widened to the intestinal microbiota as an overlooked system. The various roles of vitamin D in health and many of its receptors in every organ of the body, particularly the gut, has increased the probable role of the intestinal microbiota through vitamin-D-dependent pathways in health and disease. Therefore, vitamin-D deficiency seems to play a vital role in health due to its effect on this intestinal microbiota. Solving the vitamin-D-deficiency problem through fortification of foods is an efficient and economical solution. Fortification has long been considered as an optional and mandatory way to improve nutrient deficiencies in developed countries. Bread has a special place in the Iranian diet. It is a staple food eaten with every meal and is also economically accessible to all people in the community. Moreover, it is important to note that milk, which is frequently fortified in developed countries, is not a good carrier for fortification in Iran due to its low consumption by the Iranian people. This study was designed following two important goals; the first is the efficiency of vitamin-D-fortified bread in improving serum levels of vitamin D and the second one is to determine the effect of vitamin D on body composition, metabolic and inflammatory biomarkers, and gut microbiota in apparently healthy adults.

The current protocol has some strength including the randomized placebo-controlled clinical trial design that is the strongest empirical evidence of a treatment’s efficacy and suitable for causal inferences. The second strength is the fortification of bread in two doses, which can more accurately reflect the treatment effects. Determining the role of vitamin D and intestinal microbiota also takes place for the first time in this study and can be considered as the third strongest point of this protocol. One of the limitations of this protocol is the inability to measure the total microbiota profile of the intestine due to lack of funding. In addition, our study is a short-term study and requires more pilot studies to be carried out for community-based fortification. Moreover, our protocol is based on apparently healthy people and cannot be generalized to the patient’s community.

